**Quality assurance**

This study's quality control method includes a number of crucial steps to guarantee correctness and dependability. Participants in each group will first be thoroughly matched to the intervention groups and control group according to important clinical and demographic traits, like gender and age. To guarantee comparability across all groups, stratification will be used. The International Physical Activity Questionnaire (IPAQ) will be utilized to assess physical activity levels among control group participants. Data will be collected through interviewer-administered IPAQ during weekly check-ins. Participants in the control group who report engaging in over 150 minutes of moderate physical activity per week will be excluded from the study.

Equipment will be calibrated before each test session, and all biochemical, cardiovascular, and anthropometric index measurements will follow established testing procedures. All participants will take tests at the same time of day to reduce variability. To avoid measurement bias, the test data collector and analyst will be masked to group assignments. All testing personnel will also receive extensive training to guarantee the capability to follow the set procedures.

In order to ensure that participants complete exercises with the right form and intensity, trained exercise physiologists will oversee all training sessions. Both attendance and any sessions that are missed will be noted. Lastly, weekly progress checks will be conducted to make sure participants are performing the exercises at the recommended volume and intensity.

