Considering factors such as efficacy, cost, potential side effects, weight gain, comorbidities, and the risk of hypoglycemia, patients should prefer non-pharmacological approaches [9]. Similarly, different researchers demonstrate regular physical exercise is a fundamental component of T2DM management, demonstrably improving glycemic control and overall well-being [10-13]. Specifically, resistance training (RT) has been shown to promote skeletal muscle growth, which contributes to fat reduction [14], and improved metabolic outcomes, including lower fasting plasma glucose (FPG), enhanced insulin sensitivity, and better glucose tolerance in diabetic patients [15]. Additionally, RT benefits lipid regulation by increasing HDL-c levels and reducing triglycerides (TG), making it an effective intervention for T2DM management [16]. Similarly, a meta-analysis and systematic review reviled that, aerobic exercise has demonstrated positive effects on markers of metabolic syndrome (MetS), including reduced fasting glucose, higher HDL-c levels, and lower TG levels [17, 18], moreover, it helps reduce systolic blood pressure (SBP), diastolic blood pressure (DBP), resting heart rate (RHR), fasting blood sugar (FBS), and body mass index (BMI), while improving oxygen saturation (SpO2) compared to the control group in individuals with T2DM [19].

While both aerobic and resistance exercise have their benefits, concurrent training (CT), which incorporates the special advantages of both, is typically recommended for the treatment of type 2 diabetes. There is evidence from numerous studies that it works. Glycated hemoglobin (HbA1c), body fat, peak oxygen uptake, cholesterol, and insulin resistance (HOMA-IR) were all found to significantly improve in people receiving concurrent aerobic and resistance exercise, according to Bassi, Mendes [20]. Similarly, Ambelu and Teferi [21] found that a combined aerobic-strength program significantly lowered body composition measures, blood pressure, and fasting blood glucose. However, despite the recognized benefits of CT, research on the optimal sequencing of aerobic and resistance exercises within this training approach remains limited and inconclusive.

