**Study design**

This study adopts a two-phase sequential research design to investigate the impact of exercise sequence in concurrent training on patients with type II diabetes. Phase I involved conducting a systematic review and meta-analysis titled “Effect of concurrent continuous aerobic and short rest resistance exercise training on metabolic biomarkers in type 2 diabetes patients: a systematic review and meta-analysis.” This review aimed to summarize and synthesize existing evidence on the effects of concurrent training on metabolic outcomes such as HbA1c, insulin resistance, and lipid profile. The review identified both clinical and methodological gaps in the current literature, with a notable lack of evidence on the role of exercise sequence: specifically, whether performing aerobic training before or after resistance training and controlling confounding variable has differential effects on key metabolic and cardiovascular biomarkers in this population.

Building on the findings from the systematic review, Phase II employs a parallel-group randomized controlled trial (RCT) to address the gaps identified. The trial focuses on the sequence of exercise as a potentially important but under-researched variable in concurrent training programs for individuals with type II diabetes. Participants will be randomly allocated in equal numbers to one of three groups: the CART group (Concurrent Aerobic then Resistance Training), the CRAT group (Concurrent Resistance then Aerobic Training), and a wait-list control group (COT). Randomization will follow a 1:1:1 ratio and will be stratified by sex and age, with participants grouped into four age categories: 41–45 years, 46–50 years, 51–55 years, and 56–60 years. To reduce allocation bias, the randomization process will be overseen by the personal trainer and the principal researcher, while outcome assessments will be conducted by independent data collectors blinded to group assignment.

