$$\mathrm{THR}=HR rest + [(HR max - HR rest) \times Intensity]$$

*Equation 6 HRR approach Karvonen target heart rate formula*

Whereas:

- HR max = 220 – age
- RH: expressed the number of beats per minute (bpm) at rest.
- Intensity: the decimal representation of the desired level of exercise intensity (e.g., 0.40 for 40%, 0.60 for 60%).

The Polar H7 heart rate monitor (Polar Electro, Kempele, Finland) (Hernández-Vicente et al., 2021) will be used to continually track the participants' target heart rates as they exercise. To giving real-time feedback, this device makes sure that the intensity of the workout stays within the predetermined target heart rate range.

There will be resistance and aerobic workouts within the concurrent resistance-aerobic (CRAT) and concurrent aerobic-resistance (CART) groups. The sequence in which the resistance or aerobic components will be done first and second is the only distinction between the two training regimens (CRAT and CRAT). Every training session, there will be a 5-minute recovery and transition period in between the two training programs (aerobic and resistance components).

To ensure the detection of any adverse events, heart rate, blood pressure, and blood glucose levels will be monitored before and after each exercise session, particularly if a medical professional observes unusual or concerning patterns. It would not be possible to incorporate a placebo therapy that mimicked exercise in this investigation (Arora et al., 2023). Rather, a control group will be created in which individuals continue with their regular care regimen while abstaining from any regular exercise program. This makes it possible to compare the impact of the training program with the individuals' current diabetes control techniques.

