**Data management and statistical analysis**

All data will be systematically coded and entered into a secure, password-protected database for computer-assisted analysis. Data handling procedures include double-entry verification and regular monitoring to ensure accuracy, completeness, and consistency. Any discrepancies or spurious entries will be flagged and resolved through cross-checking with source documents.

Statistical analysis will be performed using SPSS version 27. The primary analytical approach is Repeated Measures Analysis of Covariance (RM ANCOVA), which allows for the evaluation of time-dependent changes across intervention groups while controlling for dietary practice as a covariate. This adjustment accounts for individual variability in nutritional habits that may influence metabolic outcomes.

The model will assess:

- **Main effects of time** (pre- vs post-intervention),
- **Main effects of group** (CART, CRAT, COT),

Assumptions of normality, homogeneity of variance, and sphericity will be tested prior to analysis. Violations will be corrected using appropriate statistical adjustments (e.g., Greenhouse-Geisser correction). The level of significance is set at *p* < 0.05, and partial eta squared (η²) will be reported to indicate effect sizes.

The sample size of 39 was determined through power analysis, targeting 80% power to detect moderate effect sizes in insulin resistance and cardiovascular outcomes, with a 5% significance level and allowance for 10% attrition.

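### Removing active participants after randomisation, in the control arm only, can bias the comparisons with control, plausibly but not certainly in favour of exercise

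*Protocol*

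**What the plan says.** All references are to the Protocol.

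- **Quality assurance, control arm.** The IPAQ "will be utilized to assess physical activity levels among control group participants". On timing: "Data will be collected through interviewer-administered IPAQ during weekly check-ins". The consequence: "Participants in the control group who report engaging in over 150 minutes of moderate physical activity per week will be excluded from the study".
- **Quality assurance, exercise arms.** "Both attendance and any sessions that are missed will be noted". Weekly progress checks cover training volume and intensity. No removal rule is stated for these arms.
- **Study design.** "Randomization will follow a 1:1:1 ratio and will be stratified by sex and age".
- **Exercise Training Protocol.** In the control arm, "individuals continue with their regular care regimen while abstaining from any regular exercise program".
- **Data management and statistical analysis.** The main analysis is a repeated-measures ANCOVA with dietary practice as covariate and group (CART, CRAT, COT) as a main effect. The sample size of 39 includes "allowance for 10% attrition".
- **Rationale & background information.** The protocol's premise is that "regular physical exercise is a fundamental component of T2DM management, demonstrably improving glycemic control and overall well-being".
- **Study goals and objectives.** The primary aim is the comparison of the two exercise sequences.

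**The concern.** Randomisation makes the arms comparable at entry. A rule that later drops people from one arm, because of something they did after entry, can undo that comparability if the behaviour is related to outcome. The protocol's own premise says that it is: activity improves glycaemic control. Controls who become active may therefore be those whose results would have come closest to the exercise arms. Without them, the remaining controls could look worse than the randomised control arm would have looked.

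At stake is the claim that concurrent training improves health compared with usual care, which the Project summary expects to show. The three-group test of group is also affected, because COT is one of its levels.

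**Working it through.** **1. When and where the rule acts.** It is worded for people already in the control group and triggered by a weekly interview. It is therefore a post-randomisation rule and not an entry criterion. The text states it for COT only; missed sessions in CART and CRAT are recorded without consequence.

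**2. Whether another provision repairs it.**

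- Stratification by sex and age balances the arms at entry only.
- Masked data collectors and analysts guard against measurement bias, not selection.
- The model adjusts for diet, not for activity.
- Project management mentions imputation but does not link it to these participants.
- The Follow-up section concerns safety and health status.

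**3. Arm size.** 39 / 3 = 13 per arm, so each removal costs 1/13 = 7.7% of the control arm. The 10% allowance is 0.10 × 39 = 3.9, or about four people across the whole trial. The figure of 39 cannot be firmly reproduced, because the effect is given only as moderate and no pre-post correlation is stated. The point does not depend on it.

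**4. Shift in the control mean.** Suppose k of n controls are removed and their mean change is δ better than that of the rest. The mean then shifts by (k/n) × δ. *Assumed*: k = 3, δ = 0.5 to 1.0 SD.

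- (3/13) × 0.5 = 0.12 SD
- (3/13) × 1.0 = 0.23 SD
- 3/39 = 7.7% of all randomised

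**5. The same in units of the effect.** Let D be the benefit of exercise over inactive controls, p the share of controls removed, and g the fraction of D that those removed would have gained. Keeping everyone estimates D × (1 − p × g); removal gives D. The relative inflation is 1/(1 − p × g) − 1. All values of g are assumptions.

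| Removed of 13 | g = 0.25 | g = 0.5 | g = 1.0 |
|---|---|---|---|
| 1 | 2.0% | 4.0% | 8.3% |
| 2 | 4.0% | 8.3% | 18.2% |
| 3 | 6.1% | 13.0% | 30.0% |
| 4 | 8.3% | 18.2% | 44.4% |

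**6. Under a true null.** This is a simulation of 40,000 trials with 13 per arm, unit SD and a two-sample t-test at 5%. Controls are removed when a latent activity score is high; r is the assumed correlation of that score with a better outcome. Entries are bias in SD, positive toward exercise.

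| r | 10% removed | 20% removed | 30% removed | Type I error at 30% |
|---|---|---|---|---|
| −0.3 | −0.055 | −0.106 | −0.149 | 0.060 |
| 0 | −0.001 | 0.000 | 0.001 | 0.051 |
| 0.3 | 0.057 | 0.102 | 0.148 | 0.060 |
| 0.5 | 0.098 | 0.174 | 0.246 | 0.083 |

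The sign of the bias follows the sign of r, which the protocol does not give.

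**7. Precision.** By normal approximation, for a standardised difference of 0.5 (assumed) and 13 in the exercise arm, power is 24.7% with 13 controls and 21.0% with 9. The loss is small beside the possible bias.

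**The case against.** The strongest defence is that the rule has a purpose. The control condition is abstention from a regular exercise programme, and an active control no longer represents it. That is true, but removal recovers a comparison with inactive controls only if those removed would otherwise have resembled those kept. Nor does the protocol do the same for exercise-arm participants who miss sessions.

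Four further points stand and limit the finding.

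- **Direction.** A reader might infer that every comparison with control is biased toward exercise. The protocol says nothing about who becomes active or why. Its premise about exercise makes that direction plausible; the rows for r = 0 and r = −0.3 show that it is not assured.
- **Primary aim.** A reader might infer that the sequence question is compromised. CART versus CRAT does not involve the controls and is not directly affected.
- **Silence.** A reader might infer that the excluded controls are never measured or analysed, or that activity outside sessions is unrestricted in the exercise arms. The protocol states neither. It assigns a statistical analysis plan to the statistician, and that plan is not at hand. The finding rests on the stated exclusion from the study. A later plan could define analysis sets, but it could not recover week-12 measurements if exclusion meant they were not taken.
- **Size.** The number removed and the outcome difference are assumptions. If nobody exceeds the threshold, nothing happens. The 10% attrition allowance may already be meant to include such exclusions, so they need not come on top of it.

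**Conclusion.** The point holds in this form: the protocol fixes a one-sided, post-randomisation exclusion on a behaviour that it regards as related to outcome, and nothing else in the document repairs it. The asymmetry is certain from the text. Bias toward exercise is the more plausible direction, not an established one.

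On the assumptions shown, the size runs from nothing to about a quarter of an SD, with type I error up to 0.083 against a nominal 0.05. For 3 removals of 13, the effect against control would be inflated by 6% to 30% if those removed would have gained a quarter to all of the exercise benefit. The conclusion covers the comparisons with COT and the three-group test of group, and does not extend to the comparison of sequences.

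**What to change.** Replace the exclusion sentence in Quality assurance with:

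> Control participants who report more than 150 minutes per week remain in the study, complete the week-12 assessment and are analysed in the arm to which they were randomised. The exceedance is recorded as a deviation, and an analysis without them is a sensitivity analysis only.

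Any activity cut-off for eligibility is applied before randomisation.

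Where still feasible, record activity outside the trial sessions in the same way in all three arms at the existing weekly checks. The instruction must leave out the supervised sessions: 3 × 60 minutes of main training is 180 minutes per week, already above 150, so an unmodified questionnaire would not be comparable across arms.

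**Cost.** The change to the analysis rule is a change of text. The added recording is a short questionnaire at checks that already take place, but it may come too late: the trial was registered during the intervention period, and Duration of the project places the intervention in June to August. The statistical price is some dilution of the exercise-versus-control contrast by active controls, which the sensitivity analysis would help to show.

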**Expected outcomes of the study**

This study is expected to advance scientific understanding of how exercise sequencing—specifically aerobic-resistance versus resistance-aerobic training affects cardiometabolic health in individuals with Type II diabetes mellitus (T2DM). By controlling for dietary practice and using robust statistical methods, the findings will clarify whether the order of exercise modalities influences improvements in insulin sensitivity, glycemic control, lipid profile, and cardiovascular function.

The results will be disseminated through peer-reviewed publications and conference presentations, contributing to the academic literature on diabetes management and exercise physiology. Beyond scholarly impact, the findings have practical implications for clinical care: they will inform evidence-based exercise prescriptions tailored to the needs of T2DM patients, enhancing the effectiveness of non-pharmacological interventions.

At the health system level, the study supports integration of structured, sequence-aware exercise programs into diabetes care protocols, particularly in resource-limited settings like Ethiopia. If sequence-specific benefits are confirmed, training guidelines for physiotherapists and diabetes educators can be refined to maximize patient outcomes.

From a policy perspective, the evidence may guide health authorities in developing or updating diabetes management strategies, promoting exercise as a cost-effective tool to reduce disease burden and improve quality of life. The study also aligns with broader public health goals by encouraging lifestyle-based interventions that are scalable, sustainable, and culturally adaptable.

**Dissemination of results and publication policy**

The results of this trial will be disseminated through multiple channels to maximize scientific, clinical, and community impact. Findings will first be submitted for publication in peer-reviewed scientific journals specializing in diabetes, exercise science, and clinical health. Presentations will also be made at national and international scientific conferences.

In addition to academic dissemination, results will be communicated directly to the participating patients and their families in a clear and accessible manner. Community-level dissemination will be conducted through local health centers, diabetes associations, and public forums to ensure broader awareness of the benefits of exercise interventions. Where appropriate, findings will also be shared with relevant policy-making bodies, including the Ministry of Health and regional health bureaus, to support evidence-based recommendations for diabetes management and prevention strategies.

Publication policy follows international research ethics standards. The principal investigator will take the lead in drafting and submitting manuscripts. Co-investigators who contribute substantially to the design, implementation, analysis, or interpretation of results will be included as co-authors. Data collectors, laboratory staff, and other contributors will be acknowledged appropriately in publications and presentations. No publications arising from this study will be submitted without the agreement of the research team.

**Duration of the project**

**Project Timeline**

The protocol specifies the anticipated duration of each phase of the project along with a detailed month-by-month schedule of activities. The overall project spans 9 months, beginning from January and ending with dissemination of results.

- January – February (Phase One: Systematic Review):
  - Objective: To summarize and synthesize existing evidence on the impact of concurrent training on metabolic biomarkers in individuals with Type 2 Diabetes Mellitus.
  - Activities:
    1. Conduct a comprehensive literature search across databases.
    2. Screen studies for eligibility based on pre-defined inclusion and exclusion criteria.
    3. Extract and organize data on concurrent training interventions, metabolic outcomes, and study characteristics.
    4. Critically appraise study quality and risk of bias.
    5. Identify gaps in current evidence to inform the experimental intervention.
- March – April (Phase Two: Intervention Protocol Preparation):
  - Develop detailed exercise intervention protocols for CART and CRAT groups.
  - Prepare training manuals, standard operating procedures, and data collection tools.
  - Train research staff on protocol implementation and data management.
- May: Submission and approval of ethical clearance from relevant institutional review boards.
- June – August (Phase Three: Intervention Implementation):
  - Recruit participants, conduct screening and baseline assessments.
  - Implement the 12-week supervised concurrent training program (CART and CRAT groups).
  - Monitor adherence, record session attendance, and collect ongoing data.
- September (Phase Four: Post-Intervention Assessment and Follow-Up):
  - Conduct post-intervention measurements of metabolic, cardiovascular, and anthropometric outcomes.
  - Clean and organize collected data for analysis.
- September - October: Data analysis, interpretation, and preparation of manuscripts.
- September - January: Dissemination of results to participants, the community, scientific audiences, and policy makers.

**Problems anticipated**

While the study is designed to be feasible within the proposed 12-week timeline and allocated budget, several challenges may arise during implementation. One key concern is participant retention, particularly in the intervention groups, due to time constraints, transportation issues, or health-related setbacks. To address this, flexible scheduling, regular follow-up calls, and motivational support will be provided to encourage adherence. Transportation stipends may be considered if budget permits.

Another potential difficulty is variability in dietary practices, which could confound metabolic outcomes. Although dietary practice is statistically controlled as a covariate, additional efforts will be made to monitor and reinforce consistent dietary behavior through brief nutritional guidance and regular check-ins.

Limited funding may restrict access to advanced diagnostic tools or biochemical assays. To mitigate this, cost-effective alternatives will be used where possible, and partnerships with local health institutions will be explored to access shared resources.

Data completeness and quality may also be affected by missing or inconsistent entries. This will be managed through rigorous data monitoring, double-entry verification, and early identification of discrepancies. Training sessions for data collectors and exercise supervisors will be conducted to ensure protocol fidelity.

These proactive measures aim to safeguard the integrity of the study and ensure successful delivery of outcomes within the stipulated timeframe and budget.

